## 8.3 ADVERSE EVENTS AND SERIOUS ADVERSE EVENTS

### 8.3.1 DEFINITION OF ADVERSE EVENTS

An adverse event (AE) is any untoward medical occurrence in a subject during participation in the clinical study or with use of the experimental agent being studied. An adverse finding can include a sign, symptom, abnormal assessment (laboratory test value, vital signs, electrocardiogram finding, etc.), or any combination of these regardless of relationship to participation in the study.

### 8.3.2 DEFINITION OF SERIOUS ADVERSE EVENTS

A serious adverse event (SAE) is one that meets one or more of the following criteria:

- Results in death
- Is life-threatening (places the subject at immediate risk of death from the event as it occurred)
- Results in inpatient hospitalization or prolongation of existing hospitalization
- Results in a persistent or significant disability or incapacity
- Results in a congenital anomaly or birth defect

An important medical event that may not result in death, be life threatening, or require hospitalization may be considered an SAE when, based upon appropriate medical judgment, the event may jeopardize the subject and may require medical or surgical intervention to prevent one of the outcomes listed in this definition.

---

### 8.3.3 CLASSIFICATION OF AN ADVERSE EVENT

---

#### 8.3.3.1 SEVERITY OF EVENT

The following scale will be used to grade adverse events:

1. Mild: no intervention required; no impact on activities of daily living (ADL)
2. Moderate: minimal, local, or non-invasive intervention indicated; moderate impact on ADL
3. Severe: significant symptoms requiring invasive intervention; subject seeks medical attention, needs major assistance with ADL

---

#### 8.3.3.2 RELATIONSHIP TO STUDY INTERVENTION/EXPERIMENTAL MANIPULATION

To assess relationship of an event to study intervention, the following guidelines will be used:

1. Related (Possible, Probable, Definite)
  - a. The event is known to occur with the study intervention.
  - b. There is a temporal relationship between the intervention and event onset.
  - c. The event abates when the intervention is discontinued.
  - d. The event reappears upon a re-challenge with the intervention.
2. Not Related (Unlikely, Not Related)
  - a. There is no temporal relationship between the intervention and event onset.
  - b. An alternate etiology has been established.

---

#### 8.3.3.3 EXPECTEDNESS

The Study MPIs and DSMB will be responsible for determining whether an SAE is expected or unexpected. An adverse event will be considered unexpected if the nature, severity, or frequency of the event is not consistent with the risk information previously described for the intervention.

---

### 8.3.4 TIME PERIOD AND FREQUENCY FOR EVENT ASSESSMENT AND FOLLOW-UP

Collection of adverse events will use both active and passive assessments methods.

- Active assessment will occur in two ways:
  - During our outcome measurement at 3, 9, and 15 months, will collect data regarding possible adverse events using the Unwanted Events and Adverse Treatment Reaction Checklist.

- This checklist is recommended by methodical review for resilience interventions to assess unwanted or adverse effects of the training program.
- Each month during the intervention period, we will use the 3-way messaging capabilities of our text messaging platform, or email (participant preference), to ask about possible adverse events.
  - A message asking “Over the past month. have you experienced a physical injury, distress, anxiety, or illness as a result of your participation in this study? Yes/No” will be sent. Those who do not reply will be sent a second message within 24 hours with the same text. Those that reply yes to either message will be contacted to gather additional details.
- Passive assessment will be ongoing during the intervention period. At enrollment, we will inform all participants to contact the project manager or interventionist if they think an injury or illness they have had during the study period may have occurred as a result of their participation in this study.

In our previous center-based intervention studies, no injuries related to participation have occurred. We therefore anticipate that injury risk is minimal. If such an event occurs, the project manager will collect a detailed description of the event, the adverse outcome, severity of the adverse event, and whether or not participants viewed it as related to the study. Information about the event will be shared with the MPIs and the Independent Monitoring Committee (IMCR). The IMC, as an unbiased party, will be responsible for categorizing it as: definitely unrelated, or unlikely, possibly, probably, or definitely related to study participation. Adverse event reports will be submitted to the IRB after completed by the IMC. A summary of these reports will be submitted to the project officer on an annual basis.

---

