| Adverse Event Reporting              |           |                    | X                   |                   |                   |                    |
| Follow-up and Maintenance     |           |                    |                     |                   |                   |                    |
| Director: Follow-up contact          |           |                    |                     | X                 | X                 | X                  |
| Director: Online Survey              |           |                    |                     | X                 | X                 | X                  |
| Staff: Follow-up contact             |           |                    |                     | X                 | X                 | X                  |
| Staff: Online Survey                 |           |                    |                     | X                 | X                 | X                  |
| Randomly Selected: Process Interview |           |                    |                     | X                 |                   |                    |

*Note: Survey includes Demographics, Connor-Davison Resilience Scale, General Health Questionnaire, Perceived Stress scale, Social Determinants of Health, Work Well BQ, Work Limitations Questionnaire, Absenteeism, Readiness; Follow-up: Process questions*

*Note: All contact is remote/online*

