### 8.2 SAFETY ASSESSMENTS

At enrollment, we will inform child care centers and their participating providers to contact the project manager if they feel an injury, illness or related event may have occurred to them as a result of their participation in this study. Additionally, as part of both intervention arms, participants will be texted monthly to report on any adverse events that may have occurred. If such an event occurs or is reported, the project manager will collect a detailed description of the event, the adverse outcome, severity of the adverse event, and whether or not participants viewed it as related to the study. This report will then be reviewed by the DSMB and Adverse event reports will be submitted to the IRB after completion by the DSM officer if related to participation in the study.

As required by IRB the study will also include common statements related to seeking medical care or prescreening when starting, or during, a wellness program.

For the RESILIENCE arm the following will be included in provided materials...

*The information in this program is not a substitute for medical advice. This resilience program does promote increased awareness of thoughts, emotions, and personal experiences, which may lead to moments of discomfort or self-reflection. If you experience any distress or emotional discomfort during the study, please seek the advice and counseling of a trained mental health professional. If needed, resource contacts can be provided by study staff.*

While the RESILIENCE program does have a behavior health coach, it is not intended as individual counseling for personal struggles or mental health issues. In the highly unlikely event that a staff member feels a participant is considering self-harm IRB also requires the following message be sent through email or text:

*We are sorry to hear that it has been a difficult time for you recently. If you are currently having thoughts of harming yourself, please reach out for help. Here are some options:*

- *National Suicide Prevention Hotline: Call 988 or visit <https://988lifeline.org> and use the “click to chat” feature to be connected to someone immediately*
- *Crisis Text Line: Text “HOME” to 741741*
- *BlackLine: [name]*
- *Trans Lifeline: [name]*
- *The Trevor Project: [name]*
- *Contact your primary care or mental health provider*
- *Consider going to your local emergency department*

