### 8.3.5 ADVERSE EVENT REPORTING

Summary of reporting procedures:

- Adverse Event Reports
  - If an AE occurs, the project manager will collect a detailed description of the event, the adverse outcome, severity of the adverse event, and whether or not participants viewed it as related to the study. This information will then be reviewed by the IMC, who will determine relationship to the study (definitely unrelated, or unlikely, possibly, probably, or definitely related), expectedness of the AE (expected or unexpected), and severity of the AE (mild, moderate, severe) to study participation.
  - SAE reports will be submitted by the MPIs to the IRB and NCCIH immediately after IMC review. Non-severe AEs will be reported to IRB, as required, and to NCCIH in the annual report. The monthly (MPIs), or quarterly (IMC), reports will include a summary of all AEs for review by MPIs and IMC.

---

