#### 9.4.4 SAFETY ANALYSES

N/A

---

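### The monthly and passive adverse event questions are narrower than the protocol's own definition, and no summary of adverse events by arm is planned

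*Protocol*

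**What the plan says.** Definition: Protocol section 8.3.1 counts untoward medical occurrences, signs, symptoms and abnormal findings, "or any combination of these regardless of relationship to participation in the study".

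Relatedness: section 8.3.5 sends the project manager's description of each event to the independent monitoring committee, "who will determine relationship to the study", on a scale that runs down to definitely unrelated.

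Collection: section 8.3.4 has three routes.
- A monthly text or email during the intervention asks "have you experienced a physical injury, distress, anxiety, or illness as a result of your participation in this study".
- At the 3-, 9- and 15-month surveys the study "will collect data regarding possible adverse events using the Unwanted Events and Adverse Treatment Reaction Checklist". The stated purpose is to pick up unwanted effects of the training program.
- Under a passive instruction given at enrollment, participants make contact if they think an injury or illness may be due to taking part.

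Section 8.2 words the enrollment instruction in a similar way ("an injury, illness or related event may have occurred to them as a result of their participation in this study"), but its next sentence describes the monthly text as a request for any adverse events, with no causal condition. Section 2.3.3 describes the text check as limited to events arising from the study.

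Schedule: the row "Adverse Event Reporting" in section 1.3 is marked only in the intervention column, and the survey note there does not list the checklist.

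Analysis: under "9.4.4 SAFETY ANALYSES" the only entry is N/A.

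**The concern.** The definition is causality-free and the causality decision belongs to the committee. The two routes that run during the intervention nevertheless ask the participant to make that decision first. An event that the participant does not connect with the program need not be reported by either route, so the committee may not get to classify it. This includes serious events, because no separate route asks for them.

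Other parts of the protocol assume an unfiltered count. Section 8.3.6 has a rule for unrelated serious events, section 10.1.2 monitors serious event rates in all participants, and section 10.1.6 checks adverse event rates against pre-study assumptions. Sections 8.2, 8.3.4 and 8.3.5 also record whether the participant viewed the event as related. That field says little if most reports come from people who already think so.

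Both arms are active programs with different named risks (section 2.3.1): emotional distress with the resilience program and physical injury with increased activity. A reader of the results will want events by arm, and the protocol's only statement on safety analysis is N/A.

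**Working it through.** The protocol gives no event rate, expected event count or attribution share, so there is no figure to reproduce. The check sets the sections side by side.

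| Source | Scope of events | Causal condition on the participant? |
|---|---|---|
| 8.3.1 definition | any untoward occurrence | no |
| 8.3.5 committee review | all reported events, down to definitely unrelated | no |
| 8.3.4 monthly message | injury, distress, anxiety, illness | yes |
| 2.3.3 text check | possible adverse events | yes |
| 8.2 description of the monthly text | any adverse event | no |
| 8.3.4 passive instruction | injury or illness | yes (thinks it may be due to the study) |
| 8.2 enrollment instruction | injury, illness or related event | yes (feels it may be due to the study) |
| 8.3.4 checklist at 3, 9 and 15 months | possible adverse events | none quoted; purpose is effects of the program |

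**Conflict 1: definition against collection.** The monthly message and the passive instruction are narrower than section 8.3.1. The passive wording sets a lower bar (may have) than the monthly message, but it still requires a causal suspicion. In section 8.3.4 it also names only injury or illness, so distress, the risk named for the resilience program, is not mentioned.

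**Conflict 2: one message described in two ways.** Sections 8.3.4 and 2.3.3 carry the causal condition for the monthly text. Section 8.2 does not.

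**Conflict 3: schedule against section 8.3.4.** Section 1.3 shows adverse event reporting only during the intervention, while section 8.3.4 also collects events at 3, 9 and 15 months.

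**Count of scheduled active contacts.** Assuming one message per month for 3 months, there are 3 messages + 3 checklists = 6. Three of the 6 carry the condition in their quoted wording, and the other 3 are not shown to carry it. The first checklist comes at 3 months, when the active program has ended.

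**Reach of the checklist.** It is collected at the follow-up measurements. Section 9.2 allows for 15% loss at 3 months and 20% at 15 months, and participants who are lost would not supply it.

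**Size.** If a share *a* of qualifying events is self-attributed and reported, these two routes miss 1 − *a*. If the shares are *a*₁ and *a*₂ in the two arms, equal true rates appear in the ratio *a*₁/*a*₂. The protocol gives no value for any of these, nor for what the checklist recovers, so the result could lie anywhere from no loss to a large one.

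**Analysis.** Section 8.3.5 plans event summaries for the investigators (monthly) and the committee (quarterly), and section 10.1.6 plans an annual list and summary. Section 10.1.2 speaks of rates in all participants. None states a split by arm.

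**The case against.** The strongest reply is that ascertainment does not rest on the two filtered routes alone. The checklist is a second active route with no quoted causal condition, and section 8.2 describes the monthly text as open to any event. A reader might infer that participants are asked only about events they blame on the study, and that all other events never reach the committee. The documents do not support this: the checklist may pick up some of them, and its items are not shown.

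A reader might also infer a direction of bias, on the ground that a muscle injury is easy to link to an exercise program while worsening distress is hard to link to a stress program. That is plausible but not shown. The monthly message names distress and anxiety, and section 8.2 has the resilience materials tell participants that the program may bring discomfort, which could raise attribution in that arm. Nor is there support for a number. Attribution of 50% in one arm and 20% in the other would give 0.5/0.2 = 2.5, but both inputs would be invented.

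Third, distress is compared by arm through the General Health Questionnaire (sections 3, 9.1 and 9.4.3), with no self-attribution, and events are reviewed for oversight. The trial is described as minimal risk. The survey note in section 1.3 may simply be incomplete, since it also omits the pregnancy question of section 8.3.9.

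All of this limits the point without removing it. The questionnaire compares mean scores and does not count events. Oversight summaries are not stated by arm. The wording conflicts remain, and N/A is an explicit entry, which differs from a detail left to a statistical analysis plan.

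**Conclusion.** The point holds in a limited form. The monthly message and passive instruction in section 8.3.4 are narrower than the definition in section 8.3.1 and pre-empt the committee's role in section 8.3.5. Section 8.2 contradicts section 8.3.4 on what the monthly text asks. During the intervention, events that participants do not attribute to the study can be missed by these routes, and whether the later checklist recovers them cannot be settled from the protocol. No by-arm summary of adverse events is planned.

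Under-counting is a likely consequence, not a demonstrated one, and neither its size nor the direction of any between-arm bias can be computed. The conclusion assumes that the message is sent as worded in section 8.3.4. If it is sent as section 8.2 describes, the filter applies only to the passive route, but the contradiction and the missing by-arm summary remain. The change should be made. The point does not threaten the primary analysis.

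**What to change.** - Reconcile sections 1.3, 2.3.3, 8.2, 8.3.1 and 8.3.4 so that the monthly and passive questions match the definition in section 8.3.1. Drop the causal condition, at least for injury, distress or anxiety, and serious events, and add distress to the passive instruction.
- Leave attribution to the committee. The participant's own view can still be recorded as a separate item after the event is reported.
- Mark adverse event collection at 3, 9 and 15 months in the Schedule of Activities and list the checklist in the survey note.
- Replace N/A in section 9.4.4 with a descriptive table by arm: number and proportion of participants with at least one event, with a related event and with a serious event, plus the checklist results. If the arms are formally compared, allow for clustering by center.

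The cost is edited message text, one table, and more unrelated reports for the project manager and committee to triage. Because section 6.3 keeps the investigators blinded, any by-arm version produced during the trial should go to the committee only.

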### 8.3.5 ADVERSE EVENT REPORTING

Summary of reporting procedures:

- Adverse Event Reports
  - If an AE occurs, the project manager will collect a detailed description of the event, the adverse outcome, severity of the adverse event, and whether or not participants viewed it as related to the study. This information will then be reviewed by the IMC, who will determine relationship to the study (definitely unrelated, or unlikely, possibly, probably, or definitely related), expectedness of the AE (expected or unexpected), and severity of the AE (mild, moderate, severe) to study participation.
  - SAE reports will be submitted by the MPIs to the IRB and NCCIH immediately after IMC review. Non-severe AEs will be reported to IRB, as required, and to NCCIH in the annual report. The monthly (MPIs), or quarterly (IMC), reports will include a summary of all AEs for review by MPIs and IMC.

---

### 8.3.6 SERIOUS ADVERSE EVENT REPORTING

Given the nature of the study and its relation to our prior work, we believe it is very unlikely that an unanticipated SAE will occur that is possibly related to the study intervention. That said, If such an event occurs, the project manager will collect a detailed description of the event, the adverse outcome, severity, and whether or not participants viewed it as related to the study. Information about the event will be shared with the MPIs and the IMCR. The IMC, as an unbiased party, will be responsible for

categorizing it as: definitely unrelated, or unlikely, possibly, probably, or definitely related to study participation.

- Unexpected fatal or life-threatening SAEs related to the intervention will be reported to NCCIH Program Officer, the IMC, and IRB within 3 days of the PIs becoming aware of the event. Other serious and unexpected AEs related to the intervention will be reported within time frame required by IRB.
- Anticipated or unrelated SAEs will be handled in a less urgent manner but will be reported to the IMC, IRB, and other oversight organizations in accordance with their requirements. and will be reported to NCCIH on an annual basis.
- All other AEs documented during the course of the trial will be reported to NCCIH in the annual report and in the annual AE summary which will be provided to NCCIH and to the IMC, including The Independent Safety Monitor(s) Report which will state that all AEs have been reviewed.

---

#### 8.3.7 REPORTING EVENTS TO PARTICIPANTS

Unrelated events will not be reported to participants, unless IRB asks for a specific case to be reported. When required by IRB, events considered related to study participation will be reported back to the individual involved. If deemed necessary by IRB, a general report (no identifiable info) of an SAE may be reported to all participants by email.

---

#### 8.3.8 EVENTS OF SPECIAL INTEREST

N/A

---

#### 8.3.9 REPORTING OF PREGNANCY

Being, or becoming, pregnant does not preclude childcare staff from study participation. Individuals who report being pregnant during recruitment will be asked to provide medical clearance for participation in physical activity before they are enrolled. During the study, pregnancy status will be monitored by asking participants “if they are currently pregnant” at the 0, 3, 9, and 15 month measurements time points and by asking participants to inform the project manager or interventionist if they become pregnant during the study. Current physical activity recommendations have been found to be safe for those who are pregnant. Specific recommendations and resources regarding physical activity during pregnancy and the post-partum period will be provided for all participants. Anyone reporting pregnancy will be personally informed about those resources after informing the study team about their pregnancy status.

---

### 8.4 UNANTICIPATED PROBLEMS

---

#### 8.4.1 DEFINITION OF UNANTICIPATED PROBLEMS

The Office for Human Research Protections (OHRP) considers unanticipated problems involving risks to subjects or others to include, in general, any incident, experience, or outcome that meets **all** of the following criteria:

- Unexpected in terms of nature, severity, or frequency given
  - (a) the research procedures that are described in the protocol-related documents, such as the IRB-approved research protocol and informed consent document

- (b) the characteristics of the subject population being studied;
- Related or possibly related to participation in the research (“possibly related” means there is a reasonable possibility that the incident, experience, or outcome may have been caused by the procedures involved in the research); and
- Suggests that the research places subjects or others at a greater risk of harm (including physical, psychological, economic, or social harm) than was previously known or recognized.

---

